## 6. Statistical Method

**Data processing and analysis:** The SAS software version 8.2 will be used to verify data consistency and perform statistical analysis.

**Descriptive analysis:** Descriptive analysis will be used to characterize the study sample. For categorical variables, absolute and relative frequency distributions will be used. For continuous variables, measures of central tendency (mean and median) and variability (standard deviation, upper and lower limits) will be applied.

**Inferential analysis:** Comparisons between pre- and post-treatment parameters will be analyzed using the *Wilcoxon rank-sum test* and *Student's t-test* for non-parametric and parametric variables, respectively. The *Chi-square test* and *Fisher's exact test* will be used to assess the homogeneity of categorical variables (race, hormonal status, and previous surgeries for stress urinary incontinence), as well as the absence of urinary leakage on urodynamic testing after the intervention. The *Mann-Whitney test* will be applied to assess the homogeneity and possible differences in medians of continuous variables between pre- and post-treatment groups that measure treatment success measured by the "I-QoL" questionnaire and pad test) will be assessed. For all statistical tests, a significance level of 0.05 or 5% ( $\alpha \leq 0.05$ ) will be adopted as the threshold for rejecting the null hypothesis.

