## **4. Methodology**

### **4.1 Study Design and Population:**

Prospective randomized clinical study involving 45 patients with SUI who will receive peri-urethral injection of 5 ml solution containing 100 million autologous ASCs (derived from muscle, bone marrow, or adipose tissue).

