### **4.3 Participants**

#### **Inclusion Criteria**

1. Patients with moderate stress urinary incontinence (SUI), primary and refractory to previous clinical treatments (behavioral therapy and physiotherapy), confirmed by physical examination (stress test), I-QOL questionnaire, cystometry (urodynamic study), and pad test (between 10 and 50 grams).

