#### **Exclusion Criteria**

1. Patients with anterior vaginal wall or uterine prolapse greater than stage 2 (POP-Q classification);
2. Patients previously submitted to surgical procedures for SUI correction;
3. Patients with genital malformations that prevent injection in the mid-urethral site;
4. Patients with previous pelvic radiotherapy;
5. Patients who during clinical and/or urodynamic evaluation present other diagnoses besides SUI (mixed incontinence, urge incontinence, detrusor overactivity, paradoxical incontinence, neurogenic bladder, urinary obstruction);
6. Patients who do not consent to participate in any stage of the study or who are unable to read, write, and understand the study;
7. Patients under 18 years of age.

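### Section 6 tests homogeneity on prior SUI surgery, which eligibility makes zero for every woman, and attaches only an unadjusted rank test to I-QoL and pad weight although both have baseline values

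*Protocol*

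**What the plan says.** Section 6 (Inferential analysis) says that chi-square and Fisher's exact tests "will be used to assess the homogeneity of categorical variables" and names three of these: race, hormonal status and "previous surgeries for stress urinary incontinence".

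Section 4.3, exclusion criterion 2, rules out "Patients previously submitted to surgical procedures for SUI correction". The inclusion criterion points the same way. It asks for "Patients with moderate stress urinary incontinence (SUI), primary and refractory to previous clinical treatments", and the treatments it lists are non-surgical (behavioural therapy and physiotherapy).

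Section 4.1 describes a "Prospective randomized clinical study involving 45 patients with SUI", with cells taken from muscle, bone marrow or adipose tissue. It states no allocation ratio.

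I-QoL and pad test are both part of the entry assessment (section 4.3) and are repeated one year after the procedure (section 5). Section 5 makes improvement on I-QoL the primary outcome, split at a score of 20. Section 6 offers a Wilcoxon rank-sum test or Student's t-test for pre/post comparisons in general. For I-QoL and pad test by name it gives a Mann-Whitney test, to serve both homogeneity and differences in medians. The wording of that sentence is garbled: it speaks of pre- and post-treatment groups. No covariate is mentioned.

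**The concern.** There are two separate matters.

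First, one of the three named categorical checks concerns a variable that cannot vary among eligible women. Sections 4.3 and 6 cannot both describe the same population. A reader is left unsure whether the item in section 6 is a stray or whether some women with earlier SUI surgery are expected.

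Second, homogeneity testing in a randomised trial with three cell sources makes sense only between the randomised groups, so a comparison of groups seems intended. For I-QoL and pad weight the named method makes no use of each woman's own starting value in that comparison. In a trial of 45 women, a chance imbalance at baseline would carry over into a one-year comparison, and a homogeneity p-value would not correct it. Precision that the collected data could supply would also be lost.

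**Working it through.** **Plan's own figure.** The protocol gives no power, SD, effect size or correlation, so there is nothing to reproduce.

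**Step 1: the prior-surgery test.**
- Inputs: N = 45 (section 4.1); women with prior SUI surgery = 0 (section 4.3, exclusion criterion 2). For display, take 15 per group; this is an assumption.
- Expected count in each yes cell = row total × column total / N = 15 × 0 / 45 = 0.
- The chi-square contribution (observed − expected)² / expected becomes 0/0, so the statistic is undefined. Running the test on a 3 × 2 table with an empty column returns a zero-expected-frequency error.
- Fisher's exact test: with an empty column only one table fits the margins, so p = 1 and the odds ratio is undefined. A run on a 2 × 2 table with a zero column confirms this.
- The result does not depend on the allocation ratio. The variable could be non-zero only through eligibility violations. Race and hormonal status remain testable.

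**Step 2: what baseline adjustment could be worth (illustration only).**
- Assumed inputs, none given in the documents: 15 per group, three groups, a linear model for the one-year value, equal SD at baseline and one year, and correlation r = 0.3, 0.5 or 0.7 between the two.
- Variance of the adjusted group difference relative to the one-year score alone = 1 − r².
- Variance of the adjusted difference relative to change from baseline = (1 − r²) / [2(1 − r)] = (1 + r)/2.
- 95% half-width for a difference between two groups, in SD units = t(0.975, 41) × √(2/15) × √(1 − r²), with 45 − 3 − 1 = 41 degrees of freedom. Without adjustment it is 0.737 SD.

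| r | 1 − r² | Variance cut vs one-year score | (1 + r)/2 | Variance cut vs change score | Half-width (SD) |
|---|---|---|---|---|---|
| 0.3 | 0.91 | 9% | 0.65 | 35% | 0.703 |
| 0.5 | 0.75 | 25% | 0.75 | 25% | 0.639 |
| 0.7 | 0.51 | 49% | 0.85 | 15% | 0.527 |

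**Limits of Step 2.** These formulas hold for differences in means from a linear model. They do not carry over to the proportion improved at the cut-off of 20, to a rank test, or to a within-patient pre/post comparison. For pad weight, entry is restricted to 10 to 50 g, which tends to lower r. Women who are cured would have values near zero, so a straight-line model may fit poorly.

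**The case against.** The strongest objection is that neither matter changes a result the protocol commits to. An empty test biases nothing. The requirement for primary SUI supports exclusion criterion 2, so the likeliest explanation is a stray item in section 6. All of this stands, and it keeps the contradiction minor. A reader might infer that the eligibility rule is equally in doubt, or that women with prior surgery will be enrolled. The documents do not support that: two eligibility statements agree and only the analysis list differs.

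On adjustment, the objection is that the choice of covariates is commonly left to a statistical analysis plan, which may exist and is not at hand, and that the protocol does not rule adjustment out. This is fair: silence alone would not be a finding. But section 6 does not leave I-QoL and pad test open. It names a method for them, and that method is unadjusted. A proposal to improve a stated method is therefore in order.

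Two further points stand. A reader might infer that baseline I-QoL and pad weight are ignored. They are not, since they enter the pre/post comparisons and the Mann-Whitney sentence. Nor does the empty item make the whole homogeneity check worthless, because the other variables remain. Finally, the between-group comparison is only garbled in the text, so the precision figures describe an analysis that the protocol does not spell out.

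**Conclusion.** The contradiction between section 6 and section 4.3 is certain. The prior-surgery test is undefined or returns p = 1 whatever the allocation, and the sections must be reconciled. It is an editorial correction with no effect on the primary result.

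The adjustment point holds as a recommended improvement to a stated method, not as an error in the plan. Under the assumptions in the table, the gain for I-QoL ranges from slight (r = 0.3) to substantial (r = 0.7). The documents give no value of r, so the true gain is unknown, and for pad weight it may be smaller. It would be going too far to conclude that the primary result is biased as planned, or that these percentages apply to the dichotomised primary outcome.

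**What to change.** 1. Reconcile section 6 with section 4.3 on prior SUI surgery. The simplest way is to delete that item from the homogeneity list in section 6.
2. State in section 6 that any comparison of one-year I-QoL between the randomised cell-source groups is adjusted for baseline I-QoL, and any comparison of one-year pad weight for baseline pad weight. ANCOVA would serve. A rank-based ANCOVA is an alternative if pad weights cluster near zero.

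The cost is a change of wording; no new data are needed because both baselines are already collected. The small downside is a model assumption that a plain rank test does not make, together with a possibly modest gain for pad weight.

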##### **c) Cystometry:**

The urodynamic test will be conducted using the Urosystem PL-2400 Polimed four-channel device. Cystometry will be performed with the patient in a semi-seated position using a two-way urethral catheter—one channel for bladder filling and the other for intravesical pressure measurement. Room-temperature distilled water will be infused at a rate of 40 ml/min. Abdominal pressure will be monitored using a rectal balloon. During the filling phase, when 200 ml have been infused, the patient will perform a Valsalva maneuver to determine the intravesical pressure at the moment of urinary leakage through the urethra. The test will be considered positive whenever urine leakage occurs, and the leak point pressure (LPP) will be recorded.

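### The chi-square/Fisher test of no urodynamic leakage names no comparator; run before versus after, it tests against a 0% baseline fixed by the entry rule

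*Protocol*

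**What the plan says.** Section 4.1 describes a "Prospective randomized clinical study involving 45 patients with SUI", each receiving "100 million autologous ASCs (derived from muscle, bone marrow, or adipose tissue". All women are treated; there is no untreated or sham arm, and no allocation ratio is given.

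The inclusion criterion in Section 4.3 requires moderate stress incontinence "confirmed by physical examination (stress test), I-QOL questionnaire, cystometry (urodynamic study), and pad test (between 10 and 50 grams"). Section 4.5(c) defines the cystometry result: "The test will be considered positive whenever urine leakage occurs". Section 5 schedules one repeat cystometry, at one year, and makes absence of leakage on it part of the definition of cure. The primary outcome is the I-QoL.

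The Abstract says that pre-treatment data will be compared with one-year data. The inferential paragraph of Section 6 has three relevant sentences:

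- The first concerns comparisons before and after treatment.
- The second gives chi-square and Fisher to the homogeneity of race, hormonal status and previous incontinence surgery, "as well as the absence of urinary leakage on urodynamic testing after the intervention". It names no comparator.
- The third applies the Mann-Whitney test to "possible differences in medians of continuous variables between pre- and post-treatment groups".

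All tests use "a significance level of 0.05 or 5"%. Sidedness is not stated.

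**The concern.** A sponsor following Section 6 could cross-tabulate leakage (yes/no) by time (before/after) and apply Fisher or chi-square. The before column would hold no dry women, because a woman without confirmed incontinence is not enrolled. That zero is a selection rule, not an estimate of how often such women would test dry if examined again. From that starting point women can only stay the same or become dry, so every dry repeat test counts towards a treatment effect. Natural fluctuation, variation in the test and other treatment during the year would all be credited to the cells.

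At stake is a spurious before/after p-value on one component of the cure definition, in a trial with no untreated arm to show the retest-dry rate.

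**Working it through.** The protocol gives no power calculation or expected dry rate for this endpoint, so there is no stated figure to reproduce.

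**Inputs**
- n = 45 (Section 4.1).
- Baseline dry = 0/45 (Sections 4.3 and 4.5(c), reading the listed confirmatory tests as all required).
- Alpha = 0.05 (Section 6), taken as two-sided.
- q = probability that a woman is dry at the one-year cystometry when treatment does nothing. This is an assumption; the protocol gives no value.

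**Step 1: smallest number of dry women giving p ≤ 0.05, before versus after**

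Fisher, 0/45 against k/45: two-sided p = 2 × C(45,k)/C(90,k).
- k = 5: 2 × 1,221,759/43,949,268 = 0.056.
- k = 6: 2 × 8,145,060/622,614,630 = 0.026.

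Uncorrected chi-square: X² = 90 × (45k)²/[45 × 45 × k × (90 − k)].
- k = 3: 3.10, below the critical value 3.84.
- k = 4: 4.19, p = 0.041.

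Chi-square with continuity correction also needs 6.

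Exact McNemar with k women changing, all in one direction: p = 2 × 0.5^k.
- k = 5: 0.063.
- k = 6: 0.031.

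The threshold is therefore 6/45 = 13% for Fisher and exact McNemar, and 4/45 = 9% for uncorrected chi-square.

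**Step 2: chance of reaching the threshold with no treatment effect**

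P(X ≥ c) = 1 − Σ C(45,k) q^k (1 − q)^(45−k), summed over k = 0 to c − 1, with c = 6 or 4.

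| Assumed q | Fisher or exact McNemar (6 or more) | Uncorrected chi-square (4 or more) |
|---|---|---|
| 2% | under 0.1% | 1.2% |
| 5% | 2.4% | 18.7% |
| 10% | 29.2% | 67.1% |
| 15% | 68.6% | 92.2% |
| 20% | 91.0% | 98.7% |

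**Step 3: the same test within one cell source**

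With 15 per source (assumed equal allocation), Fisher needs 5 dry (p = 0.042; 4 gives p = 0.0996). The chance of that with no effect is 0.1%, 1.3%, 6.2% or 16.4% at q = 5%, 10%, 15% or 20%.

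**Step 4: the alternative contrast**

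Comparing the one-year dry proportions across three sources of 15, with the same q in each, gives a false-positive rate of 0.03% to 4.0% (Fisher extended to three groups, the Freeman-Halton test) or 0.5% to 5.2% (chi-square) for q from 2% to 30%. The artefact is absent because no arm is fixed at zero.

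**The case against.** The strongest reply is that the comparator is inferred. The sentence assigning these tests contains no before/after wording. Race cannot change within a woman, so the homogeneity checks beside the leakage item make sense only between groups of women, and in a randomised trial of three cell sources those are naturally the sources. The leakage item is also defined only after the intervention. The phrase about pre- and post-treatment groups belongs to another sentence, another test and continuous variables. This stands: a reader might infer that the protocol commits to a before/after test of leakage, and it does not say so. Equally, it nowhere states a between-source efficacy comparison, and its general plan in the Abstract is before versus one year. Both readings remain open, and one is unsound.

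A reader might also infer that treating the same women as two independent samples is a second material fault. At n = 45 it changes little: exact McNemar rejects from the same 6 women as Fisher. Within 15 women the two differ (McNemar needs 6, Fisher 5), but the selected zero remains the main problem under either test.

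Finally, the error rates depend wholly on q. At q = 5% Fisher with 45 women stays below alpha, and with 15 per source it does so at 10% too. That also stands. The figures show what can happen, not what will.

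**Conclusion.** The point holds conditionally. The protocol leaves the contrast for this test unnamed. If it is run before versus after, it compares the one-year dry rate with a zero created by the entry rule, and 4 to 6 dry women out of 45 suffice for significance whatever made them dry. With Fisher the false-positive risk is within alpha at an assumed retest-dry rate of 5% and about 29% at 10%; with uncorrected chi-square it is already about 19% at 5%. If a between-source comparison is meant, the problem largely disappears.

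The documents do not support saying that the test will be run before/after or that its error rate is known to be inflated. The conclusion rests on n = 45 with complete follow-up, two-sided testing, leakage on cystometry being required for entry, and an assumed q. Since the I-QoL is primary and cystometric leakage is one component of cure, severity is low to moderate.

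**What to change.** Replace the leakage clause in Section 6 with a statement that absence of leakage on cystometry at one year will be reported as a count and proportion with an exact 95% confidence interval, overall and by cell source, with no p-value against baseline. Add that Fisher's exact test will be used for this endpoint only to compare the one-year proportions between the randomised cell sources.

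This is sound whichever contrast was intended. Changing only to a paired test would not be enough. The cost is one sentence and the loss of one before/after p-value; no extra data or patients are needed.

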## 7 Timeline

The estimated duration of the study is 2 years.

## 8. Evaluation and Dissemination

The results obtained will be presented at national and international conferences in the fields of Gynecology, Urogynecology, Cellular and Molecular Biology, and Regenerative Medicine. We aim to publish the manuscripts in journals with an impact factor greater than 3.0.

## 9. Other Support

This study project receives partial support from FAPESP.

